### Sample size

Allowing for potential participant attrition, the total sample size for the study is 60 (30 per arm). Sample size calculations assumed a two-tailed alpha of 0.05 and a similar baseline standard deviation between the two arms. A total sample size of 52 participants (26 per arm) would yield 80% power to observe a large treatment effect (Cohen’s d 0.8). This sample size estimation is conservative in the sense that including the baseline p-tau181 concentration in the final ANCOVA model would increase the power.

### Study procedure

#### Screening and enrollment

Informed consent will be obtained from both participants and their study partner. In cases where the participant lacks capacity to provide informed consent, their medical treatment decision maker will perform this role. Eligibility assessment will then occur. Evidence for criteria fulfilment will be based on patient and caregiver report, and documentation from medical specialists obtained prior to the visit. A Standardized Mini-Mental State Examination will be performed during the visit, prior to enrolment, to confirm a score of at least 18. Following enrolment, participants will undergo an initial safety assessment comprising both a physical examination and blood sampling. Baseline data collection will then occur.

#### Randomization

Participants will be randomized within 28 days of enrollment. The results of safety blood tests will be reviewed for clinically significant abnormalities prior to randomization. A central randomization schedule has been generated by an independent statistician who is a part of the data center at the Melbourne Brain Centre at Royal Melbourne Hospital, University of Melbourne. The randomization schedule has been programmed into an electronic case report form (eCRF) system, housed on a RedCAP platform (34, 35). Participants will be randomized in a 1:1 ratio to receive either 400 mg SAMe or matched placebo orally once per day for 180 days. Randomization will be stratified based on age at enrolment (<70 years vs ≥70 years) to minimize baseline imbalance between the treatment groups.

#### Blinding

This is a double-blind study. Treatment allocation will be coded to prevent unblinding. The unblinded randomization schedule will be kept as a secure spreadsheet accessible only to the study manager (employed by the sponsor) and by the data center coordinating the eCRF. If a participant’s intervention assignment is unblinded, the investigator will notify the sponsor within 24 hours.

### Intervention

Participants will be instructed to take the assigned treatment once a day for a period of 180 days as an adjunct to their Alzheimer’s disease standard of care. No dose reductions will be considered.

#### Dose justification

SAMe is widely available over the counter as a commercial product in tablet or capsule form. Most formulations contain 200 or 400 mg of SAMe per pill. Pure SAMe pills are distributed by over a dozen international manufacturers (Supplementary Table 1). Conversely, Australian consumers only have access to SAMe in combination with other active ingredients. The Australian Register of Therapeutic Goods lists 4 SAMe-containing supplements: 3 of these combine SAMe with B-vitamins, another contains 8 additional herbs and nutraceuticals (Table 1). The per-pill SAMe content ranges from 26.3 mg to 400 mg. All products are recommended to be dosed once daily with total daily doses between 157.8 mg and 1200 mg, with a median and mode of 400 mg (mean 472.2 mg). A review of pure SAMe products available internationally also identified 400 mg to be the most frequent recommended total daily dose (Supplementary Table 1). As such, we have selected 400 mg orally (pure form) once daily as the dose and route for this phase II trial.

**Table 1 Tab1:** SAMe-containing products listed by the Australian Register of Therapeutic Goods

**Brand name**	**Manufacturer**	**SAMe content per pill (mg)**	**Other active ingredients**	**Administration**	**Recommended total daily dosage in mg (number of pills)**
Orthoplex SAMe	Bio Concepts Pty Ltd	200	Pyridoxine, riboflavin, zinc	Oral, once daily	200–600 (1–3)
Orthoplex SAMe	Bio Concepts Pty Ltd	400	Pyridoxine, riboflavin, zinc	Oral, once daily	400–1200 (1–3)
ArthClear	BlueSkyGreenEarth Herbs Pty Ltd	26.3	Colecalciferol, curcumin, cysteine, glucosamine, manganese, quercetin, selenium, Boswellia serrata	Oral, once daily	105.2–157.8 (4–6)
SAMe 400 Complex	Nutrition Care Pharmaceuticals Pty Ltd	400	Cyanocobalamin, folic acid, pyridoxine, riboflavin, zinc	Oral, once daily	400–800 (1–2)

### Cognitive and psychological testing

Cognition will be evaluated using 7 instruments: the Standardized Mini-Mental State Examination (36, 37), Cognitive Dementia Rating (38), California Verbal Learning Test 3rd Edition (39), Montreal Cognitive Assessment (40), Digit Symbol Substitution Test (41), and the Geriatric Depression Scale (42).

### Independent Data Safety Monitoring Board (DSMB)

To compare the safety of SAMe versus placebo, interim safety analyses will be performed following the collection of the final visit data in the first 20 participants, and after 40 participants. The endpoint for this analysis will be the proportion of participants with SAEs in each arm of the trial. If there are concerns about the safety of participants, the independent DSMB will make a recommendation to the trial executive committee regarding continuing, stopping or modifying the trial. The Haybittle-Peto procedure for generating early stopping boundaries will be used (43). A recommendation for early termination due to safety reasons will be considered by the independent DSMB if the Haybittle-Peto boundary (p=0.001, Z=3) at a given interim analysis is crossed.

No interim analysis for efficacy or futility is planned.

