### Statistical analysis

All outcomes and analyses are prospectively categorized as primary, secondary or exploratory. Differences in all endpoints between the 2 arms of the study will be tested independently at the two-tailed 0.05 level of significance. All estimates of treatment effects will be presented with 95% confidence intervals. The primary endpoint will be tested using an ANCOVA model with treatment arm as an independent variable and baseline blood p-tau181 concentration as a covariate. Between group differences in secondary and exploratory outcomes will be assessed using regression models as appropriate to the response outcome distribution using baseline values of the respective outcomes as adjustment covariates. The detailed analysis will be prespecified in a formal statistical analysis plan which will be finalised prior to the study database lock.

No formal adjustments will be undertaken to constrain the overall type I error associated with the secondary and exploratory analyses. Their purpose is to supplement evidence from the primary analysis to characterize the treatment effect more fully. Results from the secondary analyses will be interpreted in this context.

Given that establishing biological efficacy is the primary objective of the trial, according to the pre-specified estimand, all participants who achieve at least 80% study medication compliance and provide a 180-day blood sample will be included in the primary efficacy analysis. All participants who provide both baseline and end of treatment blood samples will be included in a secondary dose-response analysis to account for potential early study withdrawals or poor compliance.

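### The DSMB safety boundary pairs p=0.001 with Z=3, which are different thresholds, and states no sidedness or test

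*Protocol article*

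**What the plan says.** In the protocol article, the section on the independent DSMB plans two safety looks: "interim safety analyses will be performed following the collection of the final visit data in the first 20 participants, and after 40 participants". The measure is fixed: "The endpoint for this analysis will be the proportion of participants with SAEs in each arm of the trial". The formal trigger is worded "if the Haybittle-Peto boundary (p=0.001, Z=3) at a given interim analysis is crossed", and what a crossing leads to is given as "A recommendation for early termination due to safety reasons will be considered by the independent DSMB". The section does not say whether the boundary is one- or two-sided, or which test yields the p-value or Z.

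Two other statements bear on how to read it. The Statistical analysis section sets a general convention: "Differences in all endpoints between the 2 arms of the study will be tested independently at the two-tailed 0.05 level of significance". The DSMB section also gives the board a route that does not depend on the boundary: "If there are concerns about the safety of participants, the independent DSMB will make a recommendation to the trial executive committee", covering continuation, stopping or modification of the trial.

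**The concern.** A boundary written as a p-value and a Z in one bracket reads as a single threshold in two notations. Here the two notations give different thresholds. For some interim tables a DSMB member using Z=3 would report a crossing and one using p=0.001 would not, and the text does not say which figure governs. The looks are small, about 10 and 20 per arm, so each additional participant with an SAE moves the statistic a long way. The choice between a large-sample Z and an exact p-value then matters as well. At stake is whether the formal rule gives one answer for given data.

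**Working it through.** **Inputs.** The boundary p=0.001, Z=3 and the looks at 20 and 40 participants come from the DSMB section. The two-tailed convention comes from the Statistical analysis section. The Randomization section gives the allocation ("Participants will be randomized in a 1:1 ratio"). Exactly 10 and 20 per arm is an assumption that follows from that ratio.

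**Step 1: can the stated pair be reproduced?**

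- Two-sided: 2 × (1 − Φ(3)) = 0.0027, and Φ⁻¹(0.9995) = 3.29.
- One-sided: 1 − Φ(3) = 0.00135, and Φ⁻¹(0.999) = 3.09.

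Neither reading makes Z=3 and p=0.001 equal. Two-sided, Z=3 is 0.0027 / 0.001 = 2.7 times as permissive. One-sided, 0.00135 becomes 0.001 only when rounded to three decimals.

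**Step 2: does the difference change a decision?** With a participants with SAEs on SAMe, b on placebo and n per arm, the pooled statistic is Z = [(a − b)/n] / √[p̄(1 − p̄) × 2/n], where p̄ = (a + b)/(2n).

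- 7 v 0 of 10: p̄ = 0.35; Z = 0.7 / √(0.35 × 0.65 × 0.2) = 0.7 / 0.2133 = 3.28.
- 8 v 0 of 20: p̄ = 0.20; Z = 0.4 / √(0.20 × 0.80 × 0.1) = 0.4 / 0.1265 = 3.16.

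| Split | Per arm | Pooled Z | Two-sided normal p | Two-sided Fisher p | One-sided Fisher p |
|---|---|---|---|---|---|
| 7 v 0 | 10 | 3.28 | 0.00103 | 0.0031 | 0.0015 |
| 8 v 1 | 10 | 3.15 | 0.0017 | 0.0055 | 0.0027 |
| 8 v 0 | 20 | 3.16 | 0.0016 | 0.0033 | 0.0016 |
| 10 v 1 | 20 | 3.19 | 0.0014 | 0.0033 | 0.0017 |

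All four cross Z=3, and none reaches p=0.001 two-sided. The 7 v 0 case misses by only 0.00003 on the normal approximation. By Fisher's test all four miss clearly, and they miss one-sided too.

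**Step 3: the one-sided normal reading.** Here the comparison is Z=3 against Z=3.09. Enumerating every split with an excess on SAMe gives none between the two values at 10 per arm, and only 11 v 2 and 18 v 9 (both Z=3.04) at 20 per arm. On this reading the pair nearly agrees.

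**Step 4: smallest splits that cross (SAMe v placebo).**

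| Rule | 10 per arm | 20 per arm |
|---|---|---|
| Pooled Z ≥ 3 | 7 v 0, 8 v 1 | 8 v 0, 10 v 1, 11 v 2 |
| Pooled Z ≥ 3.29 (two-sided p=0.001) | 8 v 0, 9 v 1 | 9 v 0, 11 v 1, 12 v 2 |
| Two-sided Fisher p ≤ 0.001 | 8 v 0, 10 v 1 | 10 v 0, 12 v 1, 13 v 2 |

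**Step 5: sensitivity at each look.** The document gives no expected SAE rate, so the rates below are assumptions (placebo v SAMe). Each probability comes from full enumeration of two binomials. Ranges run from Fisher p ≤ 0.001 to pooled Z ≥ 3.

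| Assumed rates | 20 participants | 40 participants |
|---|---|---|
| 10% v 30% | 0.1-0.4% | 0.8-4.6% |
| 10% v 40% | 0.4-2.4% | 5-18% |
| 10% v 50% | 2-8% | 18-41% |

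In every row, the upper figure is more than twice the lower.

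**The case against.** The strongest reply is that a harm boundary is naturally one-sided, that 0.00135 is 0.001 to three decimals, and that the pair is therefore a rounded statement of one rule. Step 3 shows that this is nearly right for a one-sided normal test. It does not settle the matter: the DSMB section never says one-sided, the article's only stated convention is two-tailed, and an exact one-sided p-value still exceeds 0.001 for all four splits in Step 2. In fairness, the article applies the two-tailed convention to endpoint tests at 0.05 and does not expressly extend it to the safety boundary.

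A second reply is that an article leaves the choice of test to the DSMB charter or the SAP. That stands for the test taken alone: its absence would not be a finding. It does not cover a threshold that the article prints, and prints inconsistently.

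A reader might go further and infer that the boundary is almost never crossed and falsely reassures the DSMB. The document does not support this. At 40 participants a very large assumed excess (10% v 50%) crosses 18-41% of the time. Low sensitivity is a property of a deliberately strict boundary at small numbers. Crossing only prompts consideration of termination, and the DSMB may make a recommendation on any safety concern without it. A reader might also infer that waiting for final-visit data leaves out participants who die or withdraw early. The article does not say so, its safety estimand covers everyone who has taken at least one dose, and the counting rule for each look is charter-level detail.

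**Conclusion.** The point holds for the threshold. As written, the boundary is two different rules, and the text gives no sidedness by which to choose between them. Under the article's two-tailed convention the gap is a factor of 2.7 in p. It changes the answer for 8 v 1 and, by a hair on the normal approximation, 7 v 0 at 10 per arm, and for 8 v 0 and 10 v 1 at 20 per arm. An exact test makes the gap wider. If a one-sided normal test was intended, the practical conflict shrinks to two splits at the second look and none at the first. The results assume equal arms at each look. The sensitivity figures also rest on assumed SAE rates; they are supporting information for the DSMB and not a separate error in the plan.

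**What to change.** Replace the bracketed pair with one internally consistent threshold, state whether it is one- or two-sided, and say that it is evaluated with an exact test suited to about 10 and 20 per arm, such as Fisher's. Which threshold to adopt is for the DSMB and sponsor to decide. As supporting material, give the DSMB a short table of the SAE splits that reach the chosen boundary at each look, with crossing probabilities over a range of assumed SAE rates, so that its low sensitivity is understood alongside the board's existing freedom to act on any safety concern.

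The cost is one sentence in the protocol and one table for the DSMB. It needs no extra participants and uses no efficacy alpha, because no efficacy or futility interim is planned. An exact test is stricter than the pooled Z at the same nominal level, so the DSMB should see the table before settling the threshold.

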### Statistical analysis

All outcomes and analyses are prospectively categorized as primary, secondary or exploratory. Differences in all endpoints between the 2 arms of the study will be tested independently at the two-tailed 0.05 level of significance. All estimates of treatment effects will be presented with 95% confidence intervals. The primary endpoint will be tested using an ANCOVA model with treatment arm as an independent variable and baseline blood p-tau181 concentration as a covariate. Between group differences in secondary and exploratory outcomes will be assessed using regression models as appropriate to the response outcome distribution using baseline values of the respective outcomes as adjustment covariates. The detailed analysis will be prespecified in a formal statistical analysis plan which will be finalised prior to the study database lock.

No formal adjustments will be undertaken to constrain the overall type I error associated with the secondary and exploratory analyses. Their purpose is to supplement evidence from the primary analysis to characterize the treatment effect more fully. Results from the secondary analyses will be interpreted in this context.

Given that establishing biological efficacy is the primary objective of the trial, according to the pre-specified estimand, all participants who achieve at least 80% study medication compliance and provide a 180-day blood sample will be included in the primary efficacy analysis. All participants who provide both baseline and end of treatment blood samples will be included in a secondary dose-response analysis to account for potential early study withdrawals or poor compliance.

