### Study Estimands

#### Primary estimand

Population: all included participants.Individual level outcome measure: percentage change in plasma p-tau181 concentration (comparing baseline to 180 days). P-tau181 levels will be measured using the single-molecule array (Simoa) technique according to the manufacturer’s instructions (Quanterix Corp., US).Population level outcome measure: difference in means between intervention and control groups adjusted for baseline p-tau181 level.

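### The primary ANCOVA omits the age stratum used in randomisation; if that stratum is prognostic, the test is conservative and some extra power is forgone

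*Protocol article*

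**What the plan says.** The Randomization section states: "Randomization will be stratified based on age at enrolment". The cut is at 70 years, the given purpose is to limit baseline imbalance between arms, and no other stratification factor is named.

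The Statistical analysis section specifies for the primary endpoint an "ANCOVA model with treatment arm as an independent variable and baseline blood p-tau181 concentration as a covariate". The Primary estimand section gives the matching summary measure: "difference in means between intervention and control groups adjusted for baseline p-tau181 level". Age is in neither.

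Secondary and exploratory outcomes get only a general description: regression models suited to the outcome's distribution, adjusted for that outcome's own baseline value. The detailed analysis is left to a statistical analysis plan that is not shown.

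The Sample size section states: "A total sample size of 52 participants (26 per arm) would yield 80% power to observe a large treatment effect (Cohen’s d 0.8"). It treats baseline adjustment as a bonus beyond that calculation.

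**The concern.** Stratified randomisation makes the arms nearly equal on the stratification factor, so the treatment estimate varies less from one hypothetical trial to the next. The usual model standard error reflects this only if the factor is in the model. If the factor predicts the outcome and is left out, its variance stays in the residual. The reported standard error then exceeds the true one, confidence intervals cover more often than 95%, and the test rejects less than 5% of the time under the null.

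In a trial of 60 people sized for a large effect, even modest precision is worth keeping when it costs one model term. The primary model's covariates are named in two places in the article, so this is a stated choice and not a detail left open.

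**Working it through.** **Inputs from the protocol article.** Two-sided alpha 0.05; d = 0.8; 26 per arm evaluable, 30 per arm randomised; 1:1 allocation (Sample size and Randomization sections). Primary model: treatment and baseline p-tau181.

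**Assumed inputs, not in the article.** Partial R² of the age stratum given baseline: 0 to 0.20. Share of participants in one stratum: 35%. Permuted blocks of 4 within stratum. The effect d = 0.8 is taken in units of the residual SD of the planned model.

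**1. Reproducing the stated sample size.** For a two-sample t test, the noncentrality is d × √(n/2).
- n = 25: 0.8 × √12.5 = 2.828, power 79.1%.
- n = 26: 0.8 × √13 = 2.884, power 80.7%.

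So 26 per arm is the exact t-test answer. The step from 52 to 60 allows for 8/60 = 13.3% attrition. No covariate enters the calculation.

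**2. Expected overstatement of the standard error.** With the stratum balanced by design, the ratio of the model SE to the true SE is about k = 1/√(1 − R²). The type I error without the stratum is then about 2 × [1 − Φ(1.96 k)].

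| Partial R² | k | 1.96 k | Approx. type I error |
|---|---|---|---|
| 0 | 1.000 | 1.960 | 5.0% |
| 0.02 | 1.010 | 1.980 | 4.8% |
| 0.05 | 1.026 | 2.011 | 4.4% |
| 0.10 | 1.054 | 2.066 | 3.9% |
| 0.20 | 1.118 | 2.191 | 2.8% |

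**3. Simulation** (52 participants, 10,000 trials per setting, ANCOVA with and without the stratum).

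| Partial R² | Type I without | Type I with | Power without | Power with | Power forgone |
|---|---|---|---|---|---|
| 0 | 5.0% | 5.0% | 79.9% | 79.8% | none |
| 0.02 | 5.3% | 5.3% | 80.6% | 81.1% | 0.5 points |
| 0.05 | 4.5% | 4.9% | 80.3% | 81.8% | 1.5 points |
| 0.10 | 3.7% | 4.7% | 81.5% | 84.2% | 2.7 points |
| 0.20 | 2.9% | 4.9% | 81.8% | 87.6% | 5.8 points |

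The Monte Carlo standard error is about √(0.05 × 0.95/10,000) = 0.2 points for type I error and √(0.8 × 0.2/10,000) = 0.4 points for power. The 5.3% at R² = 0.02 appears with and without the stratum and is simulation noise. So is 79.9% against the exact 80.7%, apart from slightly unequal arms when blocks are incomplete.

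The mechanism shows in the null runs without the stratum. At R² = 0.10 the mean model SE is 0.2791 and the actual SD of the estimate is 0.2650 (ratio 1.053). At R² = 0.20 they are 0.2797 and 0.2507 (ratio 1.116). Both agree with k.

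A second set of simulations (20,000 trials per setting) gave power without and with the stratum of 81.0 and 80.9% (R² = 0), 81.5 and 82.9% (0.05), 81.7 and 84.4% (0.10), and 83.0 and 88.3% (0.20).

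**4. Analytic comparison.** Noncentral t power with the effect scaled to 0.8 k and one further degree of freedom spent gives 80.7%, 81.5%, 82.6%, 84.6% and 88.5% down the same rows. Set against a fixed 80.7%, the last two imply gains of 3.9 and 7.8 points. That overstates the gain, because stratified allocation already makes the estimate less variable and lifts the unadjusted model's power slightly. The simulated differences are the ones to use.

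**The case against.** The strongest reply is that nothing here is invalid and the harm is hypothetical. Most of it stands.

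- **The harm depends on an unknown.** A reader might infer that the standard errors are certainly too wide. The article gives no figure for how age under 70 against 70 or over predicts percentage change in p-tau181 after baseline adjustment. At R² = 0 nothing is lost, and up to 0.05 the loss is under 2 points.
- **The design keeps its promise.** A reader might infer that the trial is underpowered. The 52 comes from an unadjusted comparison, and power without the stratum stays at about 80 to 83% in every setting examined. Only power beyond the plan is forgone.
- **Stratification is not wasted.** Its stated aim, balance between arms, is met whatever model is fitted, and part of the precision gain is kept: in the larger simulation, power without the stratum rises from 81.0% to 83.0% as R² goes from 0 to 0.20.
- **The statistical analysis plan could add the term.** For secondary and exploratory outcomes this is a good answer, since the article describes those models only in general terms. They are not faulted here.

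The last reply does not fully answer the primary analysis. Its covariates are named in the Statistical analysis section and again in the estimand, so a plan that added age would depart from both.

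Restricting the analysis to adherent participants with a 180-day sample does not remove the effect either. In a check with 8 of 60 lost at random and R² = 0.10, null rejection was 4.1%, against 4.0% without loss.

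**Conclusion.** The concern holds in conditional form. The primary model leaves out the only stated stratification factor. If that factor is prognostic after baseline, the analysis is conservative: at an assumed partial R² of 0.10 and 0.20, type I error is about 3.7% and 2.9%, so nominal 95% intervals cover about 96.3% and 97.1%. The power forgone is about 3 and 5 to 6 points. At R² = 0 neither including nor omitting the term makes a measurable difference.

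These sizes rest on the assumed R² range, a 35% smaller stratum, blocks of 4 and 26 per arm. The documents do not support a claim of inflated type I error, of a treatment estimate biased by this omission, or of a shortfall from the stated 80% power. A positive result from the planned model would be no less credible. This is a minor efficiency and coverage point, not a validity error.

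**What to change.** In the Statistical analysis section, add the randomisation age stratum (under 70 against 70 or over) as a fixed covariate in the primary ANCOVA. In the Primary estimand section, amend the summary measure so that the difference in means is adjusted for baseline p-tau181 and age stratum. Make both changes before database lock. The statistical analysis plan can carry the same term into the RBANS and other models.

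The cost is one model term and one degree of freedom. By exact calculation at 26 per arm, if age has no prognostic value, power is 80.68% with the term against 80.72% without it. No new data are needed, because the stratum must be known to randomise.
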